#### Criteria for discontinuing or modifying allocated interventions

Physiotherapists and nurses will be instructed to adapt the exercise to patience individual tolerance. This is to avoid unnecessary harm in terms of exercise-induced pain. Furthermore, patients and health personnel are taught to act and involve hospital doctors or general practitioners if medication needs to be modified.

#### Strategies to improve adherence to interventions

Adherence to interventions is monitored by the project group by telephone interview with patients every 2 weeks for the first 12 weeks after discharge. All patients will receive an exercise diary, and physiotherapists are required to fill in the progression in resistance weekly. Nurses are required to fill out a nursing diary.

#### Relevant concomitant care permitted or prohibited during the trial

No restriction on concomitant care was prohibited during the trial.

#### Provisions for post-trial care

No provisions or compensation will be paid by the trial.

### Outcome

#### Primary outcomes

The primary outcome for the physical function is Timed Up and Go [20] 8 weeks after discharge.

As the study is organised across two sectors, the CAS score measured 30 days after discharge makes a second primary outcome.

TUG is a valid and reliable test that measures the time it takes a person to get up from a chair with an armrest, walk 3 m, return to the chair, and sit [21]. The standard error of measurement (SEM) for patients with hip fractures is 11% [9]. It is hypothesised that patients in the intervention group will achieve a significantly reduced TUG score compared to usual care.

The CAS assesses mobility by (a) getting in and out of bed, (b) sit to stand, and (c) gait with a usual walking aid. It is hypothesised that a significantly larger number of patients in the intervention group will have a CAS = 6 at 30 days post-surgery compared to the control [22].

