**Methods/design:**

The project is designed as a stepped-wedge cluster randomised controlled trial. The study population of patients are older adults 65 years of age and above discharged after a hip fracture and healthcare professionals in primary and secondary care (municipalities and hospitals). Healthcare professionals from different sectors (hospital and municipalities) will be engaged in the empowerment-orientated praxis, through a workshop for healthcare professionals with knowledge sharing to the older adults using a digital health application (app). The rehabilitation intervention consists of 12 weeks of progressive resistance exercises initiated 1–2 days after discharge. To improve communication across sectors, a videoconference involving the patient and physiotherapists from both sectors will be conducted. On day, 3 after discharge, an outreach nurse performs a thorough assessment including measurement of vital signs. A hotline to the hospital for medical advice is a part of the intervention. The intervention is delivered as an add-on to the usual rehabilitation and care, and it involves one regional hospital and the municipalities within the catchment area of the hospital. The primary outcome is a Timed Up and Go Test 8 weeks post-surgery.

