### Sample size

The annual enrollment of patients with hip fractures from the six municipalities was a mean of 392. With an assumption that 50% of patients fulfilling the inclusion criteria (196 of 392), 48 patients will be available for inclusion every 3 months equal to eight patients per cluster. However, due to frailty, a 20% dropout is expected. Based on these assumptions, we expect approximately six patients per cluster every 3 months for the trial equal to a total of 330 patients.

The power calculation for the TUG is based on a reduction of 25% [36] and an estimated TUG score at discharge of 21.1 s (9.2) [37, 38]. With six patients per cluster every quarter, estimated power is 89%. Interclass coefficient [39] is 0.01, and *α* is 0.05. Thus, patient recruitment period will be 21 months.

For CAS, the power calculation is based on a 25% increase in the proportion of older adults who, 30 days post-surgery, have a CAS score = 6, power equals 90%.

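### The abstract names one primary outcome and the body names two, each powered separately with a single undivided alpha of 0.05 and no stated rule for trial success.

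*Protocol article*

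**What the plan says.** In the abstract (Methods/design) the primary outcome is singular: "The primary outcome is a Timed Up and Go Test 8 weeks post-surgery".

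The section Primary outcomes has a plural heading. It starts with TUG ("The primary outcome for the physical function is Timed Up and Go") and then adds that "the CAS score measured 30 days after discharge makes a second primary outcome", giving as its reason that the study spans two sectors. Each outcome has its own significance hypothesis:

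- TUG: "patients in the intervention group will achieve a significantly reduced TUG score compared to usual care".
- CAS: "a significantly larger number of patients in the intervention group will have a CAS = 6 at 30 days post-surgery".

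The section Sample size treats the two in separate paragraphs. The TUG paragraph opens with "The power calculation for the TUG is based on a reduction of 25" per cent, gives power of 89%, and says that the intracluster coefficient "is 0.01, and *α* is 0.05". The CAS paragraph begins "For CAS, the power calculation is based on a 25% increase in the proportion of older adults who" reach a score of 6 and gives power of 90%. It states no alpha and no control proportion.

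The sections under Statistical methods (main analyses, interim analyses, additional analyses, non-adherence and missing data) contain no success rule, testing order or division of alpha.

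**The concern.** A reader of the abstract expects the trial to stand or fall on TUG. A reader of the body sees two outcomes of equal rank, each with its own hypothesis and its own power. These lead to different definitions of a positive trial, and the choice between them decides both the false-positive rate and the chance of success:

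- If either outcome suffices, each tested at 0.05, the chance of at least one false claim exceeds 5%.
- If both are required, the error rate is safe, but the chance of success is lower than either published power figure.
- If TUG is tested first, the error rate is safe and the TUG figure stands, but CAS depends on TUG.

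The article does not say which applies. The stated TUG power is informative because it shows how much alpha the sample size gave to TUG.

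**Working it through.** **Inputs**
- Difference: 25% of 21.1 s = 5.275 s. SD 9.2 s, intracluster correlation 0.01, six patients per cluster per quarter, TUG power 89% (Sample size).
- Six clusters: two municipalities split into two each, and four combined into two (Study setting).
- Seven three-month periods: 21 months / 3 (Sample size, Trial design).
- Assumed: one cluster crosses at each step (the design figure is not available) and tests are normal. Sidedness is not stated in the article.

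**1. Reproduce the 89% for TUG (Hussey–Hughes variance)**

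Between-cluster variance: τ² = 0.01 × 9.2² = 0.8464. Cell-mean variance: σ² = 0.99 × 9.2² / 6 = 13.966.

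With I = 6 clusters and T = 7 periods, U = 21 treated cells, W = 91 (sum of squared period totals) and V = 91 (sum of squared cluster totals):

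Var = Iσ²(σ² + Tτ²) / [(IU − W)σ² + (U² + ITU − TW − IV)τ²]

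- Numerator: 6 × 13.966 × (13.966 + 5.925) ≈ 1666.7
- Denominator: 35 × 13.966 + 140 × 0.8464 ≈ 607.3
- Var ≈ 2.744, SE ≈ 1.657, and 5.275 / SE ≈ 3.184

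| Alpha for TUG | Power |
|---|---|
| two-sided 0.05 | Φ(3.184 − 1.960) = 89.0% |
| one-sided 0.05 | Φ(3.184 − 1.645) = 93.8% |
| two-sided 0.025 | Φ(3.184 − 2.241) = 82.7% |

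Of these, only the undivided two-sided 0.05 gives the published figure.

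**2. CAS**

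The alpha behind the 90% cannot be recovered, because the control proportion is missing and the 25% may be absolute or relative. With an absolute increase of 25 points, six patients per cell and two-sided 0.05, power is 80%, 79%, 82%, 88% and 96% for assumed control proportions of 0.3, 0.4, 0.5, 0.6 and 0.7.

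**3. If either outcome suffices, each at two-sided 0.05**

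Independent tests: 1 − 0.95² = 9.75%. With bivariate normal statistics:

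| Assumed correlation | Family-wise error |
|---|---|
| 0 | 9.75% |
| 0.3 | 9.5% |
| 0.5 | 9.1% |
| 0.8 | 7.8% |

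**4. If both are required**

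There is no inflation. Joint power is 0.89 × 0.90 = 0.801 under independence; positive correlation would raise it.

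**5. If TUG is tested first**

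TUG keeps two-sided 0.05 and its 89%, and family-wise error stays at 5%.

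**6. If Holm is used**

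At the 0.025 step TUG power is 82.7%. If CAS passes 0.025, TUG may be tested at 0.05. Taking the CAS 90% to be at two-sided 0.05, its power at 0.025 is Φ(1.960 + 1.282 − 2.241) = 0.84. With independent tests, overall TUG power is 0.827 + (0.890 − 0.827) × 0.84 ≈ 88%.

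**The case against.** The strongest reply is that this is a condensed article and that success rules for two primary outcomes are commonly set in a statistical analysis plan, which is not shown. Silence about the rule is therefore not itself an error. That much stands. It does not remove the disagreement between the abstract and the outcome section, nor the fact that the published TUG power uses the whole 5%. An analysis plan that split alpha would contradict that figure.

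A reader might infer that both outcomes are planned at 0.05 and that the trial can therefore claim success at nearly twice the nominal error rate. The document does not support this. Alpha is written for TUG only, and no either-outcome rule is stated. The 9.75% also needs independence, which is the least plausible case because both outcomes measure mobility in the same patients.

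A reader might also infer that the sponsor is free to decide afterwards whether CAS was primary. That goes too far. The body names CAS as a second primary in advance, with a reason, a threshold and a power statement. The Discussion's emphasis on the 8-week time point suggests that TUG leads, but it sets no formal order.

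**Conclusion.** The point holds as an inconsistency with a measurable consequence. The number of primary outcomes differs between abstract and body, and the published power figures fit only some of the possible success rules. An either-outcome rule at 0.05 each would give a family-wise error of 7.8% to 9.75% for assumed correlations from 0.8 down to 0. A both-required rule would give joint power of about 80% under independence. Only a TUG-first sequence leaves the 89% intact with error at 5%, and the article does not state one.

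The TUG reproduction assumes one cluster crossing per step. The error rates assume that CAS would be tested at 0.05, the only level given. Because the rule is open rather than stated wrongly, this is something that should be fixed, not proof of an inflated error rate.

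**What to change.** Make the abstract and the outcome section agree on the number and rank of primary outcomes, and state the success rule before the outcome data are analysed. The options are:

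- **Fixed sequence (simplest).** Test TUG first at two-sided 0.05, and test CAS = 6 confirmatorily at the same level only if TUG is significant. This matches the abstract and keeps TUG power at 89%. The cost is that CAS has no confirmatory claim if TUG fails, which weakens the two-sector reason for including it.
- **Two alternative primaries.** Use Holm. Restate TUG power as 83% at the 0.025 step, and as about 88% overall if the tests are independent and the CAS 90% is at two-sided 0.05.
- **Both required.** No alpha split is needed. State joint power of about 80% under independence.

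Under any option, give the alpha and the control proportion behind the CAS power. Every option is a change of wording and restated power, with no additional patients or assessments unless the sponsor wishes to recover the lost power.

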#### Secondary outcomes

*Physical function* will also be measured using the New Mobility Score (NMS, 0–9) and the 30-s sit-to-stand test (30s-CST). The NMS assesses the patients’ gait inside, outside, and during shopping [23], and the 30s-CST is a valid test that assesses lower body strength [24, 25].

*Activities of daily living* will be measured using Barthel-20 (0–20), which is a validated tool used to assess the patients’ need for help to perform activities of daily living [26].

#### Other outcomes

*Physical function* is measured using handgrip strength (HGS) which is a biomarker for ageing [27].

*Activities of daily living* will be measured using composite physical function (CPF, 0–24). CPF assesses the patients’ need for help to basic and instrumental activities of daily living [28].

*Pain* will be assessed using the 4-point Verbal Rating Scale (VRS, no pain, slight pain, moderate pain, and severe pain) [29].

*Readmission* will be measured 30 days after discharge.

*Mortality* will be assessed as an event 30 days after discharge and within the first year.

*Quality of life and pain* will be measured using the EuroQol Five-Dimension Questionnaire [30]. EQ-5D is a standardised questionnaire, used to assess the patients’ health-related quality of life and function [31].

*Empowerment* will be assessed using the patient activation measure (PAM) [32]. PAM includes thirteen questions addressing prevention and lifestyle changes.

*Fatigue* will be assessed using the Brief Fatigue Inventory (BFI) [33].

*Collaboration between health professionals* will be assessed using a questionnaire designed by Joint Action Analytics to measure the relational capacity [34] The questionnaires will be distributed before workshops and 3 months after the workshop.

*Costs information* will be collected for a cost-utility analysis [35]. Data from registries, municipalities, and hospitals are gathered retrospectively while information on carers’ and volunteers’ expenses in assisting the older adult in activities of daily living is gathered prospectively.

Costs information and information on the number of supervised training sessions, activity level, pain, place of rehabilitation, and the number of self-training sessions will be collected every 2 weeks for 12 weeks. The patients will be equipped with a diary as a memory aid.

### Participant timeline

A timeline and a description of the specific data collected at each time point are presented in Table 3.

**Table 3 Tab3:** Forms and procedures adapted from the SPIRIT 2013 explanation and elaboration: guidance for protocols of clinical trials [11]

Time point			Post allocation							
Activity/assessment	Enrolment −***t***_**1**_	Allocation, 0	In-hospital, ***t***_**1**_	2 weeks, ***t***_**2**_	4 weeks, ***t***_**3**_	8 weeks, ***t***_**3**_	12 weeks, ***t***_**4**_	6 months, ***t***_**5**_	12 months, ***t***_**6**_	Event
Eligibility screen	X									
Informed consent	X									
Allocation		X								
Demography			X^a^							
TUG			X^a^			X	X	X		
CAS			X		X					
Barthel-20			X			X	X	X	X	
NMS			X			X	X	X	X	
HGS			X^a^			X	X	X	X	
30s-CST			X^a^			X	X	X	X	
EQ 5D			X			X	X	X	X	
CPF			X			X	X	X	X	
VRS			X	X	X	X	X	X	X	
PAM			X^a^			X	X	X	X	
BFI						X	X	X	X	
Care			X	X						
Co-morbidity			X							
Bioimpedance			X				X			
Operation			X							
Re-operation										X
Re-admission										X
Mortality										X

Care covers early detection of illness, complications, and pain management, e.g. blood pressure, pulse, respiratory frequency, saturation, consciences, temperature, and saturation

*TUG* Timed Up and Go, *CAS* Cumulated Ambulation Score, *Barthel-20* Barthel 20-Item Index, *NMS* New Mobility Score, *30s-CST* 30-s Chair Stand Test, *EQ 5D* EuroQol-5 domain, *CPF* composite physical function, *HGS* handgrip strength, *VRS* Verbal Rating Scale, *BFI* Brief Fatigue Inventory

^a^ Marked will be measured at discharge

### Sample size

The annual enrollment of patients with hip fractures from the six municipalities was a mean of 392. With an assumption that 50% of patients fulfilling the inclusion criteria (196 of 392), 48 patients will be available for inclusion every 3 months equal to eight patients per cluster. However, due to frailty, a 20% dropout is expected. Based on these assumptions, we expect approximately six patients per cluster every 3 months for the trial equal to a total of 330 patients.

The power calculation for the TUG is based on a reduction of 25% [36] and an estimated TUG score at discharge of 21.1 s (9.2) [37, 38]. With six patients per cluster every quarter, estimated power is 89%. Interclass coefficient [39] is 0.01, and *α* is 0.05. Thus, patient recruitment period will be 21 months.

For CAS, the power calculation is based on a 25% increase in the proportion of older adults who, 30 days post-surgery, have a CAS score = 6, power equals 90%.

### Recruitment

All older adults admitted to the ortho-geriatric ward will be assessed for inclusion consecutively by data collectors.

### Assignment of interventions: allocation

Randomisation will be done in advance using a balanced Internet-based randomisation list [40].

### Concealment method

Randomisation will be performed by opening a sequentially numbered opaque envelope every 3 months. A person with no patient contact and unfamiliar with the project will undertake this job.

### Implementation

After agreeing to participate, patients are assigned pending on home addresses. Patients’ home address will be concealed until informed consent was obtained and prefracture baseline data collected. The data collector will inform the patient of the assigned group.

### Assignment of interventions: blinding

#### Who will be blinded

Blinding is not possible as the health professionals need to know the older adults who are citizens in municipality randomised to intervention. Due to the visibility of intervention, it is not possible to blind the assessor either.

#### Unblinding

Not applicable.

### Data collection and management

#### Plans for assessment and collection of outcomes

Data collectors collect data in-hospital, and at 8 weeks, 12 weeks, and 6 months through home visits. Inter-rater reliability will be investigated. To promote data quality, assessors are trained and data collections forms and “how to” guides will be developed.

#### Plans to promote participant retention and complete follow-up

Only health professionals in the primary sector assigned for the workshop will have contact with the older adults assigned for intervention. At the time of the procedure, the project group will ensure that the collection of data at admission and 8 weeks later is not performed by the same project assistant, and the same applies for the following collection of data. In case of dropout, the reason for this will be examined.

#### Data management

To promote data quality and secure data, data collectors will use iPads and enter the data directly in secured servers. Every 3 months, the project manager perform completeness checks, and the entire project group is instructed to be aware of the data quality.

#### Confidentiality

The participants will be allocated an individual trial identification number, and the participant’s data will be stored on secured servers in accordance with national laws. The data will only be accessible to members of the project group.

#### Plans for collection, laboratory evaluation, and storage of biological specimens for genetic or molecular analysis in this trial/future use

This trial does not involve collecting biological specimens for storage.

## Statistical methods

### Statistical methods for primary and secondary outcomes

In the descriptive analyses, intervention, and controls will be described and compared to assess homogeneity. Categorical variables will be compared using the chi-square tests and Student’s *t*-test, or log-rank test will be used for continuous variables depending on the distribution (normal or not).

The effect of the intervention for continuous variables will be assessed using a linear mixed model with a random effect for each cluster and a fixed effect for each step of the stepped wedge model.

Categorical and ordinal data will be analysed using either a logistic or an ordinal logistic model. The experiences of the healthcare professional will be examined with a paired Student’s *t*-test.

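### The stated TUG and CAS models include no patient covariate although pre-fracture data are collected before allocation is revealed: valid, but precision is given up; separately, log-rank is the wrong test for baseline variables

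*Protocol article*

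**What the plan says.** All references are to the protocol article.

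- **Effect models** (Statistical methods for primary and secondary outcomes). Continuous outcomes use a "linear mixed model with a random effect for each cluster and a fixed effect for each step of the stepped wedge model". For the rest, "Categorical and ordinal data will be analysed using either a logistic or an ordinal logistic model"; this covers the second primary outcome, CAS = 6 at 30 days. Neither sentence names a patient covariate. The sections on additional analyses and on non-adherence and missing data add none.
- **Baseline comparison** (same section). In the descriptive analyses, "intervention, and controls will be described and compared to assess homogeneity". Chi-square tests are planned for categorical variables and, besides the t-test, a "log-rank test will be used for continuous variables depending on the distribution (normal or not").
- **Timing of baseline data** (Implementation). The patient's "home address will be concealed until informed consent was obtained and prefracture baseline data collected". The address decides the patient's cluster and so the group.
- **Table 3** (Participant timeline). NMS, Barthel-20 and CPF are in-hospital measures without a footnote mark. TUG, handgrip strength (HGS), the 30-s chair stand test (30s-CST) and demography carry the footnote "Marked will be measured at discharge". The whole in-hospital column stands in the post-allocation block.
- **Blinding** (Who will be blinded). For assessors, "it is not possible to blind the assessor either".

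**The concern.** Habitual function, age and sex are natural candidates to predict walking performance after a hip fracture. A model with cluster and step terms alone leaves whatever they explain in the residual error. Each cell of the design holds about six patients, so the mix of frail and fit patients can easily differ between control and intervention periods by chance. Nothing in the stated model adjusts the estimate for such a difference. The data needed are at least partly in hand before the group is known, so the precision could be had at almost no cost.

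The baseline paragraph raises a second, smaller issue. The log-rank test compares censored event times and does not apply to age or to a function score that is not normally distributed. As written, the homogeneity tests also take no account of cluster or calendar step, and no action is tied to their result.

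**Working it through.** **Inputs from the protocol**

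- Six clusters: two municipalities split into two each, and four combined into two (Study setting).
- Step length three months (Trial design) and 21 months of recruitment (Sample size), so 7 quarterly periods.
- Six patients per cluster per quarter, TUG 21.1 s (SD 9.2), reduction 25%, intraclass correlation 0.01, α 0.05, stated power 89% (Sample size).

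**Assumptions.** One cluster crosses per step (Fig. 1 is not shown), α is two-sided, and a normal approximation is used.

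**1. Reproducing the stated power without covariates**

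Difference: 0.25 × 21.1 = 5.275 s.

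Total variance: 9.2² = 84.64. Between-cluster variance: τ² = 0.01 × 84.64 = 0.8464. Variance of a cell mean within cluster: s² = 0.99 × 84.64 / 6 = 13.966.

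The standard stepped-wedge variance (Hussey–Hughes) for I clusters and T periods is

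Var = I s² (s² + Tτ²) / [(IU − W) s² + (U² + ITU − TW − IV) τ²].

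Here U is the number of treated cells, W the sum over periods of the squared number of treated clusters, and V the sum over clusters of the squared number of treated periods.

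- I = 6, T = 7, U = 1 + 2 + … + 6 = 21, W = V = 1 + 4 + … + 36 = 91.
- Numerator: 6 × 13.966 × (13.966 + 5.925) ≈ 1666.7.
- Denominator: (126 − 91) × 13.966 + (441 + 882 − 637 − 546) × 0.8464 = 488.8 + 118.5 = 607.3.
- Var ≈ 2.744, SE ≈ 1.657 s.
- Power = Φ(5.275 / 1.657 − 1.960) = Φ(1.224) ≈ 0.890.

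This matches the stated 89%. The sample size therefore agrees with the unadjusted model.

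**2. Effect of covariates on TUG**

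If covariates explain a share R² of the variance and the intraclass correlation stays at 0.01, both variance components shrink by (1 − R²), so SE = 1.657 × √(1 − R²). The protocol gives no R²; the range is assumed.

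| Assumed R² | SE (s) | Power for 5.275 s |
|---|---|---|
| 0 | 1.657 | 89.0% |
| 0.09 | 1.580 | 91.6% |
| 0.20 | 1.482 | 94.5% |
| 0.30 | 1.386 | 96.8% |

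Without covariates, 91.6% would need between 6.5 patients per cell (91.0%) and 7 (92.7%), and 96.8% would need nine (96.8%).

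The gain matters more if the true effect is smaller than planned. For an illustrative 3.5 s, power is 56.1% unadjusted and 60.1% at R² = 0.09.

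**3. Baseline tests**

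With ten independent baseline variables tested at 0.05 (an assumed number), the chance of at least one false signal is 1 − 0.95¹⁰ ≈ 0.40. Such a result would say nothing about whether the effect estimate needs adjusting.

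**The case against.** The strongest reply is that nothing in the model sentence is wrong. Cluster and step terms are a standard analysis of this design, and the power calculation matches it. Chance imbalance is part of the sampling error that the standard error already reflects. The article is condensed, and a statistical analysis plan that is not shown may list covariates. The gain rests on an assumed R², and 89% power is no shortfall.

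Most of this stands, and it rules out several stronger readings:

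- **That the primary analysis is invalid, biased or underpowered.** It is not; step 1 shows model and sample size agree.
- **That baseline tests are planned instead of adjustment.** The protocol places the tests among the descriptive analyses and does not link them to the effect model.
- **That pre-fracture NMS is certainly available before allocation is revealed.** The Implementation section speaks of pre-fracture baseline data without naming the measures, and Table 3 puts NMS, Barthel-20 and CPF in the post-allocation block without calling them pre-fracture values. That NMS is among them is an inference.
- **That the log-rank error harms the effect estimate.** It concerns the descriptive tables only, and may be a slip for the rank-sum test.

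The reply does not remove the point itself. The protocol states the terms of its model, and they leave out information the trial collects before the group is known. Naming covariates now is a concrete improvement on that model, whether or not an unseen plan lists some.

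Adjustment also has a cost. In a logistic model, covariates turn the CAS odds ratio into a conditional one, which is a different quantity from the unadjusted odds ratio. Recruitment began on 01 October 2020 and assessors are not blinded, so the change must be documented before anyone analyses outcomes.

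**Conclusion.** The point holds as a worthwhile gain in precision over a valid model. Under an assumed R² of 0.09–0.30, the standard error for TUG falls from about 1.66 s to 1.58–1.39 s and power rises from 89% to about 92–97%. Adjustment would also remove from the estimate chance differences in the chosen covariates, which are plausible with six patients per cell.

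These figures assume one cluster crossing per step, six patients per cell, a two-sided test, a normal approximation and an unchanged intraclass correlation of 0.01. They apply to TUG only; no corresponding figure is derived for CAS.

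The log-rank statement is an error in the text as it stands. It is minor and changes no effect estimate.

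**What to change.** 1. **Covariates.** Pre-specify age, sex and one pre-fracture function score as fixed covariates in the TUG and CAS models. NMS is a candidate once the investigators confirm that it is recorded as a pre-fracture value before the address is revealed. Age and sex cannot be altered by treatment, so the discharge mark on demography in Table 3 is no obstacle.
2. **What to leave out.** Do not adjust the primary analysis for discharge TUG, HGS or 30s-CST. They are measured after allocation and could already reflect in-hospital treatment.
3. **CAS reporting.** State that the adjusted odds ratio is conditional, and report a standardised risk difference beside it.
4. **Baseline table.** Describe baseline by condition without significance tests. If tests are kept, replace log-rank with the Wilcoxon rank-sum test.
5. **Timing.** Record the change as a dated amendment before the data are analysed. If the statistical analysis plan already lists covariates, bring the two documents into agreement.

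No new data are needed once the timing of the function score is confirmed. The cost is the amendment and the extra explanation for CAS.

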**Discussion:**

Using a stepped-wedge design, the intervention will be assessed as well as implemented in hospital and municipalities, hopefully for the benefit of older adults after hip fracture. Furthermore, the collaboration between the sectors is expected to improve.

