### Trial design

The protocol describes a cluster randomised stepped-wedge trial. It has a superiority design, a 1:1 allocation ratio, and the time interval for each step is set to three months, as illustrated in Fig. 1. The study protocol follows the Standard Protocol Items: Recommendations for Interventional Trial (SPIRIT) checklist (see Additional file 1) [10, 11]. A trial registration dataset is reported in Table 1.

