## Methods

### Study setting

The trial will involve a regional hospital in Denmark and all six municipalities in the hospital’s catchment area. The municipalities serve a mixed urban and rural population. Two of the municipalities will be divided into two clusters, and four smaller municipalities were combined to two clusters to account for the unequal population size. Services within hospitals and municipalities are free of charge in Denmark, and the responsibility for rehabilitation is shared between sectors [12]. At the time of discharge, older adults with a medically assessed need for rehabilitation are offered a referral for municipal rehabilitation [12]. A list of study sites can be obtained on request from the corresponding author.

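### The paired t-test for staff treats their changes as independent across six clusters and cannot separate the workshop from calendar change

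*Protocol article*

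**What the plan says.** The section on statistical methods for primary and secondary outcomes gives two different treatments. For continuous variables, the effect of the intervention is assessed "using a linear mixed model with a random effect for each cluster and a fixed effect for each step of the stepped wedge model". For staff it says: "The experiences of the healthcare professional will be examined with a paired" Student's t-test, with no cluster or step term.

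Only one staff outcome is described. In the Other outcomes section, collaboration between health professionals "will be assessed using a questionnaire designed by Joint Action Analytics to measure the relational capacity", and on timing: "The questionnaires will be distributed before workshops and 3 months after the workshop". The protocol does not say in so many words that the paired test is meant for this questionnaire. It is the only staff measure, though, and its two-occasion form fits a paired test.

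The abstract includes healthcare professionals in the study population, and its discussion paragraph says that "the collaboration between the sectors is expected to improve". The article gives no staff numbers, standard deviation, ICC or target effect for this outcome.

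**The concern.** The workshop belongs to an intervention introduced cluster by cluster. Staff of one municipal cluster share roll-out timing, local organisation and colleagues. The questionnaire measures working relationships, so it is plausible that colleagues' scores move together. A paired t-test counts every person's change as a separate piece of evidence. With only six clusters, even modest correlation among changes makes its standard error too small.

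The second issue is time. Under the stated schedule, no staff member is measured twice without a workshop in between. The mean change is therefore workshop effect plus whatever else changed over those months. The protocol allows for this with patients, through the step effect, and its main discussion names unequal exposure to seasonal trends as a drawback of the design.

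At stake is how far a reported improvement in collaboration could be trusted. The test is named in the plan, so this is a stated choice that fits the design poorly and not a detail left to a later document.

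**Working it through.** **The plan's own figures.** None exists for the staff outcome. The stated TUG power does confirm the layout used below.

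- Clusters: "Two of the municipalities will be divided into two clusters, and four smaller municipalities were combined to two clusters", so 2 × 2 + 2 = 6.
- Periods: "the time interval for each step is set to three months" and "Thus, patient recruitment period will be 21 months", so 21 / 3 = 7 periods, taken as one cluster crossing at each of six steps.
- Other inputs (Sample size section): 6 patients per cluster and quarter, SD 9.2 s, ICC 0.01, difference 25% of 21.1 s = 5.275 s, alpha 0.05 (taken as two-sided).

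The Hussey-Hughes variance is K·s²(s² + T·t²) / [(KU − W)s² + (U² + KTU − TW − KV)t²]. Here s² = 9.2² × 0.99 / 6 = 13.97, t² = 9.2² × 0.01 = 0.846, K = 6, T = 7, U = 21 and W = V = 91. The standard error is 1.657 s, and power is Φ(5.275 / 1.657 − 1.96) = 89.0%, against 89% stated.

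**Clustering of staff changes.** With m staff per cluster and ICC r of the change scores, the true standard error of the mean change exceeds the paired t-test's by about √(1 + (m − 1)r). For example:

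- m = 5, r = 0.01: √1.04 = 1.02
- m = 20, r = 0.10: √2.90 = 1.70

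In the last case the true error of a nominal 5% test is roughly 2[1 − Φ(1.96 / 1.70)] = 25%.

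Simulation (20,000 runs per setting, 6 clusters, no true change) gave this true error for the paired t-test:

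| Staff per cluster (assumed) | ICC 0 | ICC 0.01 | ICC 0.05 | ICC 0.10 |
|---|---|---|---|---|
| 5 | 5.1% | 5.3% | 7.1% | 9.8% |
| 10 | 5.1% | 5.8% | 10.0% | 15.2% |
| 20 | 5.0% | 7.1% | 15.8% | 25.3% |

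A t-test on the six cluster mean changes stayed between 4.8% and 5.3% in every setting.

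**What pairing already removes.** Let the scores have ICC ρ, let a share c of the cluster variance be stable over time, and let the remaining within-person correlation be w. With total score variance 1, the cluster part of the change has variance 2ρ(1 − c) and the individual part 2(1 − ρ)(1 − w). The change-score ICC is the first divided by their sum. With w = 0.6 (assumed):

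- c = 1: the change-score ICC is 0 for any ρ.
- ρ = 0.05, c = 0.8: 0.02 / (0.02 + 0.76) = 0.026.
- ρ = 0.10, c = 0.5: 0.10 / (0.10 + 0.72) = 0.122.

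**Calendar change.** With no workshop effect, change-score ICC 0 and an assumed common drift of 0.2 SD of the change, the paired t-test is significant in 19%, 34% and 59% of trials with 5, 10 and 20 staff per cluster. This does not depend on any ICC, because the test has nothing with which to separate the two sources.

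**The case against.** A reader might infer that the plan credits any before-after drift to the intervention, or claims too much for collaboration. The text does not support that. It reserves the effect of the intervention for the mixed model and says only that staff experiences will be examined. Collaboration ranks below the primary and secondary outcomes, the stated objective concerns older adults, and the abstract voices an expectation about collaboration, not a hypothesis to be tested. This stands. The fair criticism is that the test cannot separate the sources of change, not that the plan asserts a cause.

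A reader might also infer that the interval is certainly too narrow. That is not shown. Stable differences between clusters cancel in the pairing, and with uncorrelated changes the test holds its level. The only ICC in the article is 0.01, and it is for TUG. Carried over to the change scores as an assumption, it gives 5.3% to 7.1%, which is close to nominal.

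The drift of 0.2 SD is demanding if it means a steady calendar trend. Over six successive windows it adds up to 6 × 0.2 = 1.2 SD. The drift percentages therefore only illustrate the point.

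Finally, the professionals come from the hospital as well as the municipalities, while clusters are formed from municipalities. Staff of the single hospital belong to no cluster, so the six-cluster calculation does not describe them. This also stands, and the fix has to allow for it.

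None of this makes a test that assumes independent changes, with no time term, a good match for a cluster roll-out.

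**Conclusion.** The point holds in a limited form and is minor. The named test has no protection against correlated changes within six clusters, and its mean change cannot be read as the effect of the workshop. Whether its error rate is inflated depends on a change-score ICC that the article does not give. The true error is about 5% if that ICC is 0 and reaches 25% at 0.10 with 20 staff per cluster. Staff numbers, ICC and drift are all assumptions. Applying the test to the collaboration questionnaire is a natural reading but is not stated. No conclusion on TUG or CAS depends on it.

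**What to change.** Replace the sentence on the paired test with one that does the following:

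- Names the relational-capacity questionnaire as the outcome.
- Analyses each municipal staff member's change score with a random cluster effect and a small-sample correction for six clusters (for example Kenward-Roger), or uses a t-test on the six cluster mean changes.
- Treats hospital staff as a separate unit or reports them separately.
- States that the result is an uncontrolled before-after comparison and does not estimate the intervention effect.

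A mixed model on the raw before and after scores with only random intercepts for cluster and person would not do. Both intercepts cancel in the difference, so for complete pairs it returns the paired t-test's standard error. On raw scores, a random cluster-by-time term is needed.

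The change takes a few lines and no new data beyond each respondent's cluster. The cost is a wider interval even if there is no clustering. For the cluster-mean test the critical value is 2.57 on 5 degrees of freedom. The paired test has 2.05 with 30 staff (29 degrees of freedom) and 1.98 with 120 staff (119), so the ratio is 2.571 / 2.045 = 1.26 to 2.571 / 1.980 = 1.30.
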